### Safety Results from a Completed PrEP Trial

Peterson et al. conducted a randomized placebo controlled clinical trial of daily oral TDF 300mg versus placebo for HIV prevention in West African women. Nine-hundred thirty six HIV-negative women at high risk of HIV infection were observed for 428 person years for safety outcomes including monitoring of liver function tests, renal function, and clinical adverse events. No significant differences were evident between treatment groups in clinical or laboratory safety outcomes. Among the 368 participants on TDF, none had grade 3 or 4 transaminase elevation or grade 2 or higher creatinine. One TDF recipient had self-limited grade 3 decreased phosphate. Two HIV infections were diagnosed in participants randomized to TDF (0.86 per 100 person-years) and six in participants receiving placebo (2.48 per 100 person-years), yielding a rate ratio of 0.35 (95% confidence interval = 0.03-1.93), which did not achieve statistical significance. This study provides important and reassuring information on the safety of TDF chemoprophylaxis in HIV-uninfected women.

Several additional studies examining the safety and efficacy of oral tenofovir or emtricitabine/tenofovir in diverse populations are underway or in the later stages of planning.

These are shown in the table 3.2.7.

**Table 3.2.7 PrEP clinical trials currently planned or underway**

| **Sponsor** | **Product** | **Location** | **N** | **Study population** | **End date** |
| --- | --- | --- | --- | --- | --- |
| CDC | Oral TDF | Thailand | 2400 | Male/female IDU | 2010 |
| CDC | Oral TDF | USA | 400 | MSM | 2009 |
| CDC | Oral FTC/TDF | Botswana | 2000 | Heterosexual men & women | 2010 |
| NIH | Oral FTC/TDF | Andes, US, other sites | 3000 | MSM | 2010 |
| NIH | Vaginal TFV  Oral TDF  Oral FTC/TDF | Africa | 4200 | Women | 2012 |
| FHI | Oral FTC/TDF | Africa | 3900 | Women | 2012 |
| UW | Oral TDF  Oral FTC/TDF | Africa | 3900 couples | Serodiscordant couples | 2011 |

# STUDY OBJECTIVES

## Primary Objectives

- To determine the impact of varying dosing patterns on tenofovir concentrations in hair among HIV-negative men and women under conditions of modified directly observed therapy
- To determine how individual pharmacokinetic parameters influence tenofovir hair concentrations and modify the relationship between dose and tenofovir hair concentrations.

## Exploratory Objectives

- To determine the correlation between intracellular tenofovir diphosphate concentrations and tenofovir levels in hair under varying dosing patterns
- To determine dose and intracellular concentrations of tenofovir sufficient to render cells non-permissive for HIV-1 replication in vitro
- To determine the correlation between TFV scalp hair and pubic hair concentrations

# STUDY DESIGN

This is a phase 1, open label cross-over study to evaluate the impact of varying dosing patterns on concentrations of TFV in hair among a cohort of 24 HIV-uninfected men and women. In addition, the study will determine how individual PK parameters at steady state impact TFV hair concentrations.

## Expected Duration of Enrollment and Subject Participation

The approximate time to complete study enrollment is expected to be -12 months. Study participants will be followed over a 5-9 month period. The time of total study duration is expected to be approximately 6-10 months.

## Description of Study Population

The study population will include 24 generally healthy HIV-negative men and women age 18 or older. This study will plan to enroll 12 men and 12 women to provide PK data in both biologic sexes.

## Inclusion Criteria

Men and women must meet all of the following criteria to be eligible for inclusion in the study:

- Age 18 or older
- Willing and able to provide written informed consent
- Ability to speak English
- HIV-1 uninfected based on HIV rapid testing performed during screening and enrollment
- Calculated creatinine clearance ≥ 60 mL/min by the Cockcroft-Gault Creatinine Clearance Formula where creatinine clearance in mL/min is calculated as follows:

Male: [(140 - age in years) x (wt in kg)] / [72 x (serum creatinine in mg/dL)]
Female: [(140 - age in years) x (wt in kg) x 0.85] / [72 x (serum creatinine in mg/dL)]

- Serum creatinine less than or equal to the site laboratory upper limit of normal (ULN)
- Urine dipstick with negative or trace result for both glucose and protein
- Negative urine ß-HCG test (for women)
- Adequate hepatic function (total bilirubin and hepatic transaminases (ALT and AST) ≤ 2x ULN)
- Adequate hematologic function (absolute neutrophil count ≥ 1,500/mm^3^, platelets count ≥ 100,000/mm^3^, and hemoglobin ≥ 10 g/dL)
- Ability to participate in modified directly observed dosing of study drug
- Able to provide a personal cell phone number to be contacted on for unobserved mDOT visits
- Minimum length of 3 cm scalp hair in occipital region
- Willing to provide hair and plasma samples per protocol
- Dark hair (brown or black) assessed by the study clinician.
- Reproductive status: A volunteer who was born female must:
  - Agree to consistently use effective contraception from at least 21 days prior to enrollment through the last protocol visit for sexual activity that could lead to pregnancy. Effective contraception is defined as using any of the following methods:
    - Condoms (male or female) with or without a spermicide
    - Diaphragm or cervical cap with spermicide
    - Intrauterine device (IUD)
    - Hormonal contraception, or
    - Successful vasectomy in the male partner (considered successful if a volunteer reports that a male partner has [1] documentation of azoospermia by microscopy, or [2] a vasectomy more than 2 years ago with no resultant pregnancy despite sexual activity post-vasectomy);
  - Or not be of reproductive potential, such as having reached menopause (no menses for 1 year) or having undergone hysterectomy, bilateral oophorectomy, or tubal ligation
  - Or be sexually abstinent.
- Volunteers who were born female must also agree not to seek pregnancy through alternative methods, such as artificial insemination or in vitro fertilization until after the last scheduled protocol visit

## Exclusion Criteria

- Active and serious medical problems including cardiac or pulmonary disease, diabetes requiring hypoglycemia medications, previously diagnosed malignancies expected to require further treatment, and serious infections
- Hepatitis B surface antigen positivity or detectable Hepatitis B DNA in individuals who have isolated Hepatitis B core antibody positivity (HBSAg negative, anti-HBs negative, anti-HBc positive)
- History of chronic renal disease
- Known osteoporosis, osteomalacia, or osteopenia; history of pathological bone fractures not related to trauma
- Receiving ongoing therapy with any of the following: antiretroviral therapy, interferon or interleukin therapy, aminoglycoside antibiotics, amphotericin B, cidofovir, systemic chemotherapeutic agents, other agents with significant nephrotoxic potential, other agents that may inhibit or compete for elimination via active renal tubular secretion (e.g., probenecid), and/or other investigational agents
- Evidence of a gastrointestinal malabsorption syndrome or chronic nausea or vomiting which may confer an inability to receive an orally administered medication
- Use of hair dyes or hair permanent products in the last 3 months (streaking is acceptable)
- Current participation in any other research study involving drugs, investigational agents, or medical devices
- Per participant report, breastfeeding at screening or enrollment
- Active alcohol or drug use considered sufficient by clinician to hinder compliance with study procedures
- Elevated risk of HIV infection, including:

***Anyone*** *who has had one or more of the following risk factors* ***within the past 6 months****:*

- Used IV drugs recreationally
- Had vaginal or anal intercourse with HIV-infected partner(s);
- Had vaginal or anal intercourse with IDU partner(s) who injected drugs in the last 6 months
- Had syphilis, gonorrhea, non-gonoccocal urethritis, chlamydia, and/or pelvic inflammatory disease diagnosed or treated, based on self-report
- Had vaginal or anal intercourse with more than four partners of the opposite sex; and/or
- Exchanged sex for money, drugs, services, or gifts

***Man or male-to-female (MTF) transgender*** *who* ***within the past 6 months*** *has:*

- Had unprotected anal intercourse with 2 or more (male or transgender) sexual partners;
- Had anal intercourse with 4 or more male or MTF partners; and/or
- Used methamphetamines or cocaine at the time of anal intercourse with a male or MTF partner
- At enrollment, has any social or medical condition that, in the investigator’s opinion, would preclude provision of informed consent, make participation in the study unsafe, complicate interpretation of study outcome data, or otherwise interfere with achieving the study objectives

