We therefore plan to conduct a 24 week open-label study of healthy HIV-uninfected volunteers to evaluate the effects of varying dosing patterns on TFV levels in hair. We will recruit students, faculty, and staff from an academic medical center who will likely understand the importance of PK studies and can be readily accessed in a central location. In this proof-of-concept study, we will restrict enrollment to individuals with untreated, naturally dark (brown or black) hair to reduce between-person variability, making hair levels more effective at distinguishing different adherence levels and patterns. Since many PrEP trials are taking place in developing countries where individuals have dark hair, our results will be applicable to studies in these countries as well as in many international treatment settings. This study utilizes a cross-over design in which each individual undergoes three 6 week conditions in random order: 7 doses/week (100% adherence), 4 doses/week (57% adherence), and 2 doses/week (29% adherence). These levels are chosen to represent excellent adherence, moderate adherence, and poor adherence, respectively. We will employ modified directly observed therapy (mDOT), an adherence intervention shown to be effective in improving virologic and immunologic outcomes in HIV treatment studies.^19-21^ This method will provide a high level of certainty that drug is actually being taken by the study population. The relatively short duration of this study and careful safety monitoring of this trial will minimize the risk of toxicity among study volunteers.

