After written informed consent is obtained, participants will receive a symptom- directed medical and physical exam, a rapid HIV test, and screening safety laboratory tests (CBC, electrolyte panel, serum creatinine, liver function tests, total serum lipase, phosphorus, hepatitis B surface antigen, hepatitis B core antibody, hepatitis B surface antibody, urinalysis, and urine pregnancy test for women). Individuals who have isolated hepatitis B core antibody positivity will also have Hepatitis B DNA testing. Laboratory tests that fall outside the eligibility range may be repeated once within the screening period based on clinician discretion. All potential participants will receive standardized pre- and post-test risk reduction counseling and HIV testing by an FDA-approved commercially available whole blood rapid HIV test. Reactive rapid HIV test results must be confirmed with both another FDA-approved EIA and Western blot (WB) or immunofluorescent assay (IFA). Subjects will be assessed for eligibility by the research clinician and PI according to the eligibility criteria listed in sections 5.3 and 5.4. To ensure adequate hair at each sampling, participants will be advised to leave at least 2 cm of hair growth when getting their hair cut during this study.

If the participant is unable to complete all the screening procedures in one visit, they may return for one or more visits to complete these procedures.

| **Screening visit (up to 45 days prior to Enrollment visit)** | |
| --- | --- |
| Component | Procedure/Analysis |
| Educational/  Administrative | - Review educational materials/study flipchart with participant - Obtain written informed consent for screening - Assign Screening ID - Collect demographic information - Collect locator information - Assess eligibility - Provide reimbursement for visit - Schedule screen 2 and/or enrollment visit |
| Clinical | - Collect medical history - Record list of concomitant medications - Perform symptom-directed physical exam - Provide counseling   - HIV pre- and post-test counseling |
| Urine | - Collect urine sample   - Qualitative hCG   - Dipstick UA (and full UA with microscopy if greater than trace protein, glucose, heme, or leukocytes) |
| Blood | - Collect blood samples   - Complete blood count   - Serum chemistries   - Liver function tests   - Total serum lipase   - Hepatitis B testing   - HIV-1 rapid test (confirmatory testing as needed) |

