## Criteria for Suspension of Study Product

Participants will be discontinued from receiving further study tablets for the following reasons:

- Confirmed HIV-1 infection
- Positive pregnancy test
- Positive hepatitis B surface antigen test or detectable Hepatitis B DNA
- Concurrent illness which, in the investigator’s opinion, may be exacerbated by continued product administration, requires treatment which is contraindicated by the protocol, jeopardizes further compliance or follow-up, or may confound the interpretation of adverse events
- Unacceptable toxicity, as defined in the toxicity management section of the protocol
- Participant request to discontinue for any reason
- Any clinical or social situation that, in the opinion of the investigator, jeopardizes compliance with the study product or confounds the interpretation of clinical adverse events

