## Hair Specimens

Hair specimens will be collected at enrollment and on the last day of each 6-week dosing period. A standard questionnaire will be completed at each hair collection visit to record information about hair treatments and type and number of hair samples collected. Hair specimens will be used to determine tenofovir hair concentrations under each dosing condition. Hair collection will be conducted by study staff trained on proper hair collection technique and will be stored at room temperature in aluminum foil in a secured, dark location until analyzed. Scalp hair will be collected on all study participants.

Participants will also be asked to provide a pubic hair specimen on an optional, opt-in basis using a self-collection technique. Pubic hair TFV level testing could be useful in certain parts of the world (e.g. sub-Saharan Africa) where men and women shave their heads or in individuals who dye their hair. Evaluating the correlation between scalp and pubic hair TFV concentrations will help determine whether pubic hair TFV testing could be a possible substitute for scalp hair in situations where scalp hair is unavailable. Those participants who agree to hair collection would be shown a sample of 200 pubic hairs and the proper technique for self-collection, including placement of a sticker on the distal end of the hair, cutting hair as close to the skin as possible, and placing hair in aluminum foil for storage.

All hair and blood samples (see sections 8.6 – 8.8) will be run in batch after all samples have been collected. The hair and pharmacology laboratory staff will remain blinded to the dosing condition until all testing is completed.

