## Study Primary Endpoint and Predictor Variables

Consistent with the primary study objectives, the following primary endpoint will be assessed:

- Tenofovir hair concentration: Tenofovir hair levels will be determined from a specimen containing 150-200 hairs collected at enrollment and on the last day of each period. For each participant, absolute hair levels and ratios of hair levels between conditions (7 vs. 4 doses/week, 4 vs. 2 doses/week, and 7 vs.2 dose/week) will be determined.

The following will be primary predictor variables:

- Dosing condition: The dosing condition will be examined as an ordinal variable: 2, 4, and 7 doses/week. We will also use actual percentage of total doses (by directly observed recorded doses and self-administered recorded doses) taken over the 6 week period as a continuous predictor of hair levels.
- PK parameters: The primary predictor variable of total exposure (PK contribution) will be oral clearance (CL/F). This variable is estimated by the equation “dose/AUC,” where AUC is the area under the plasma-concentration time curve for each intensive PK sampling procedure. Other parameters of drug exposure that will be evaluated as predictor variables include the concentration at the end of the dosing interval (trough or C_min_), peak plasma level (C_max_), and AUC alone. These PK variables will be calculated using non-compartmental methods.

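### The hair-treatment restriction ends at entry and is looser than the background states, so scalp hair dyed or permed during the study can enter the primary endpoint

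*Protocol*

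**What the plan says.** Section 3.1 (Background) gives the design premise: "we will restrict enrollment to individuals with untreated, naturally dark (brown or black) hair to reduce between-person variability". The sentence goes on to say that this should help hair levels separate adherence levels.

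Two eligibility rules carry this out. Section 5.3 requires "Dark hair (brown or black) assessed by the study clinician". Section 5.4 excludes "Use of hair dyes or hair permanent products in the last 3 months (streaking is acceptable".

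After entry, the only hair-care instruction shown is in 7.3: "participants will be advised to leave at least 2 cm of hair growth when getting their hair cut during this study". Section 8.6 adds a record: "A standard questionnaire will be completed at each hair collection visit to record information about hair treatments".

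The endpoint is defined in 10.1: "Tenofovir hair levels will be determined from a specimen containing 150-200 hairs collected at enrollment and on the last day of each period". Absolute levels and between-condition ratios are both derived from those specimens. Section 10.3 also plans to count how often a level under a lower dosing frequency exceeds one under a higher frequency.

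**The concern.** The premise and the criteria disagree. Streaked hair is not untreated hair, and neither 5.3 nor 5.4 asks that the dark colour be natural or that the hair be untreated beyond a 3-month look-back. Staff enroll from 5.3 and 5.4, so the premise in 3.1 is not what gets enforced.

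The more practical gap is timing. The dye and perm rule looks backward from entry, while every sample that carries study drug is taken after entry. A participant may dye or perm between two collections without departing from anything visible in the protocol. Other entry rules are carried forward: contraception applies through the last visit (5.3), and starting an exclusionary medication on study has a stated consequence (9.8). Hair treatment has no counterpart.

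Each participant contributes one scalp sample per regimen. If one of the three changes for a reason other than dose, both ratios that use it change, and the crossover does not cancel this because the other two samples are unaffected. What is at stake is extra scatter in the ratios, and the reliability of overlap counts that depend on extreme values.

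**Working it through.** **1. Premise against rules.**

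- Colour: 3.1 says naturally dark; 5.3 says dark, on the clinician's assessment.
- Treatment: 3.1 says untreated; 5.4 excludes dyes and perms for 3 months and accepts streaking.
- After entry: 7.3 gives haircut-length advice only; 8.6 records treatments. The seven grounds in 7.10, introduced by "Participants will be discontinued from receiving further study tablets for the following reasons", do not mention hair. They concern dosing, and I do not suggest that they should mention it.

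**2. Timing.** Inputs: three 6-week periods and breaks of at least 3 weeks (6.2); total follow-up of about 36 weeks (section 10, opening paragraph).

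- Minimum length: 3 × 6 + 2 × 3 = 24 weeks, which reproduces the 24 weeks in 3.1.
- Breaks implied by 36 weeks: (36 − 18) / 2 = 9 weeks each.
- Gap between consecutive collections: 3 + 6 = 9 weeks at the shortest schedule, 9 + 6 = 15 weeks at the longest.
- Look-back: 3 months is about 13 weeks, all of it before entry. It covers none of the 24 to 36 weeks.

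The Protocol Summary gives 20 to 36 weeks. Twenty weeks would need breaks of (20 − 18) / 2 = 1 week, against the 3-week minimum. Nothing here depends on that figure.

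**3. Size, on stated assumptions.** The documents give no figure for the effect of treatment on tenofovir in hair. Assume that levels are proportional to dosing frequency, so the true 7:4 ratio is 7/4 = 1.75, and that a fully treated specimen loses a fraction L of its drug, with L from 0.20 to 0.50. Both are assumptions made for illustration.

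One participant's ratio:

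- Daily-dosing sample treated, 1.75 × (1 − L): 1.75 × 0.8 = 1.40; 1.75 × 0.5 = 0.88.
- 4-doses sample treated, 1.75 / (1 − L): 1.75 / 0.8 = 2.19; 1.75 / 0.5 = 3.50.

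Geometric mean ratio over 24 participants with one daily-dosing sample treated, 1.75 × (1 − L)^(1/24):

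- L = 0.20: 0.8^(1/24) = 0.991, giving 1.73.
- L = 0.50: 0.5^(1/24) = 0.972, giving 1.70.

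The average moves by about 1 to 3%, while the single ratio moves by 20 to 50% downward, or 25 to 100% upward.

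**4. Overlap counts.** Under the same proportionality, a treated daily-dosing sample drops below that person's own 4-doses sample once 1 − L < 4/7, that is, L above 43%. The counts in 10.3 compare levels across participants as well, so a smaller loss could be enough for someone whose levels are already low. Section 10.4 treats little or no overlap among 24 subjects as the result that would support hair as a marker, so one altered sample matters more here than in a mean.

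**The case against.** Several points on the other side are sound.

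- **The background is rationale, and 5.4 is the rule.** Permitting streaks is an explicit choice. This stands as far as it goes: the defect there is a mismatch in wording, and it could be cured from either side.
- **Treatment before entry mostly concerns hair formed before the first dose.** It cannot have removed drug that was not yet deposited. A reader might infer that the 3-month look-back is too short, or that pre-entry streaks distort on-drug levels. The documents support neither inference.
- **It is noise, not directional bias.** All six sequences are used with four participants each (7.5), so every regimen appears equally often in every period. Treatment unrelated to regimen therefore favours no regimen by design. Section 10.3 also reports medians and geometric means and plans bootstrap checks. This stands for averages. It helps less with overlap counts or with any one person's ratio.
- **Treated samples can be identified, and their handling may be planned elsewhere.** The questionnaire in 8.6 flags them. How they are analysed may be in a statistical analysis plan that is not shown, and advice to participants may be in consent pages that were removed. I therefore make no finding on analysis handling, and say only that no visible section restricts treatment on study.
- **Section 8.6 is not a rule about this trial.** It says pubic hair testing might be useful in places "where men and women shave their heads or in individuals who dye their hair". This shows that the authors saw dyed scalp hair as a difficulty for the method in future use. It gives no size and sets no condition for these participants.

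What remains is the mismatch between 3.1 and 5.3/5.4, and the absence of an on-study instruction.

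**Conclusion.** The point holds in a limited form. The stated premise of untreated, naturally dark hair is not what the criteria enforce, and the dye and perm restriction stops before any on-drug sample is taken. Treatment between collections could alter one of a participant's three samples, add scatter to within-person ratios, and possibly produce false overlap.

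It would go too far to conclude that the primary result is biased. Ratios are only part of the primary endpoint, beside absolute levels. The 20 to 50% loss is an assumption without support in the protocol, and the number of participants who would treat their hair is unknown. Even on that assumption, a single affected daily-dosing sample shifts the mean 7:4 ratio only from 1.75 to between 1.73 and 1.70. Streaking would probably affect only some of the 150 to 200 hairs, so its effect would be smaller still. The case for acting is that the correction is nearly free and protects the analyses most sensitive to one sample.

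**What to change.** 1. Reconcile 3.1 with 5.3 and 5.4: use the same description of eligible hair in all three, and state whether streaked hair counts as untreated.
2. In 7.3, beside the haircut advice, add an instruction not to dye, bleach, streak or perm scalp hair from enrollment through the last hair collection.
3. In 8.6, state that where streaks are present the occipital specimen is taken from unstreaked strands where feasible.

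The existing questionnaire then serves to check adherence to the instruction, so no new form or visit is needed. The cost is a wording amendment, a minor burden on participants over 24 to 36 weeks, and a slightly narrower pool of volunteers.
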